***Content Validation***

The content has been validated by an expert panel and BC patients. The expert panel comprises two oncology nurses, with at least five years’ experience in oncology nursing, an oncologist, a psychologist, a mental health nurse and a research professor. Comments from the experts were obtained with respect to accuracy, adequacy and appropriateness of the intervention content. Two patients undergoing BC chemotherapy will be invited to comment on the content of the intervention to ascertain that the contents of the intervention will be easily understood by the patients.

***Intervention format***

PEIs can be delivered through various formats, including individual, group, home, hospital, or community-based (Moore et al., 2021; Sin & Norman, 2013). For this study, as evidence from the systematic review conducted suggested that PEIs delivered through the mobile phone might be beneficial in resolving certain psychological issues in this population; the intervention will be delivered through a mobile phone. Similarly, as the intervention is multi-component, a combination of individual and group formats will be employed. The BC education, coping skills training and discussion components will be delivered on a group basis; psychological support and nurse-led consultation will be delivered on an individual basis. Furthermore, the intervention will be community-based as chemotherapy in Nigeria is delivered on an out-patient basis.

***Intervention duration***

A duration of six weeks will be considered as evidence from a previous study suggest that online PEI delivered for six weeks might be effective in improving psychological outcomes (Lepore et al., 2014).

***Intervention dosage***

The dosage which include amount, frequency, and duration of the intervention (Manojlovich & Sidani, 2008; Reed et al., 2007) will depend on the component of the intervention concerned. BC education and discussion will each be delivered for 30 minutes per week as this was an average duration and frequency found among previous studies in the systematic review earlier conducted. Stories from BC survivours will be delivered 15 minutes per week on the first, third and fifth weeks. Coping skills training will be incorporated into the BC education that will be delivered for a period of three weeks. Amount, frequency and duration of psychological support and nurse consultation will be 15-20 minutes call first week, third week and fifth week by oncology nurses from the research team.

***Intervention delivery***

To ascertain consistency of the intervention, all sessions of the BC education and coping skills training will be delivered by the principal investigator. Similarly, all discussion sessions will be moderated by the principal investigator. The BC education session will be held every Monday for 30 minutes which will be followed by a discussion forum for 30 minutes.

***Technical Support***

The research assistants will train the intervention group for 30minutes on how to install and use the app. Participants will be given the telephone number of the developer so they can call in case of any technical issue that needs to be fixed during the application usage. They can also drop a text message, or a voice note for the developer. Technical assistance will be provided 8:00am to 5:00pm from Monday to Friday.

**Piloting of the Intervention**

***Aim and Objectives***

The pilot study is aimed at testing the acceptability and feasibility of the mPEI programme for addressing psychological issues of Nigerian women undergoing BC chemotherapy and identifying participants’ comments on the programme.

The specific objectives are to: (i) test the acceptability and feasibility of using the mPEI programme and study procedures; (ii) evaluate the recruitment capability; (iii) explore participants’ comments on the intervention; and (iv) utilise the findings for amendment of the intervention for the main study.

***Design***

An assessor-blinded, two-arm RCT using a parallel group will be adopted. Qualitative data will also be collected from an online focus group discussion to assess the acceptability, perceived usefulness, and ease of usage of the intervention.

***Sample Size Planning***

According to Kato (2020), a sample size of 15-20 per group is appropriate for ensuring scientific validity of a smartphone-application based pilot study; hence, for this study, 15 participants will be utilised for intervention and control groups, respectively.

***Setting***

The pilot study will be conducted in Lagos University Teaching Hospital which is one of the centres used for the qualitative study described earlier.

***Inclusion criteria***

These will include females who: (1) are between age 18-70 (2) are newly diagnosed with BC within the recent three months; (3) currently receiving chemotherapy; (4) have access to a smartphone and internet; (5) are able to read and write in English; (6) are cognitively capable of completing the questionnaires; and (7) consent to join the study.

***Exclusion criteria***

These will be those women with a concurrent physical or mental illness (as these might act as a confounder); cognitively impaired; are older than 70 years of age as aging barriers have been noted in mhealth usage with older adults (Wildenbos et al., 2018).

***Research assistant training***

Two research assistants (RAs) that were previously trained in qualitative data collection will be further trained for one hour on subject recruitment and quantitative data collection using the data collection instruments. Their ability to properly administer the instruments will be tested through interrater reliability.

**Intervention Group**

Participants in the intervention group will receive the mPEI programme for six weeks alongside the standard care they receive in the hospital.

**Control Group**

Participants in the control group will receive only the standard care in each hospital which entails routine care by doctors and nurses during their clinic attendance. Standard care is the control condition in the study. For each hospital, standard care will entail routine care by doctors and nurses during their clinic attendance. The standard care involves regular instructions on chemotherapy, side effects and general health education. The education takes place around 15 minutes during each clinic attendance.

***Outcome measures***

Data will be collected from the intervention and control group at baseline, and immediately after the completion of the intervention. All the instruments will be administered in English language which is the medium of instruction for the intervention.

*Self-efficacy for coping with cancer*

Self-efficacy for coping with cancer will be measured with the Cancer Behavior Inventory-Brief Version (CBI-B). The instrument comprises 12-items measuring confidence of individuals in performing activities that show how well they are coping with the demands of cancer and their treatment. Each item will be scored on a nine-point Likert scale with ‘1’ meaning ‘not at all confident’ and ‘9’ meaning ‘totally confident’. Higher scores indicate greater self-efficacy in coping. This instrument has been used in BC studies. It has also been validated and found reliable with a Cronbach’s α coefficient ranging from .84 to .88. (Heitzmann, 2001). (See Appendix C).

*Coping*

Coping will be assessed with Coping Orientation to Problems Experienced Inventory (Brief COPE). The scale can measure primary coping styles under three subscales: problem-focused coping, emotion-focused coping and avoidant coping. This 28-item instrument was developed as a short version of the original 60-item COPE scale (Carver et al., 1997). The 28 items are measured on a four-point scale (ranging from1= I haven’t been doing this at all, 2= a little bit, 3= a medium amount, and 4= I’ve been doing this a lot). The instrument has also been verified among patients with breast cancer receiving chemotherapy and have a fairly good reliability and validity. Internal consistencies ranged from 0.25 to 1.00, and intraclass correlation coefficient ranged between 0.05 and 1.00 (Yusoff et al., 2010). (See Appendix D).

*Anxiety and Depression*

Anxiety and depression will be assessed with the Hospital Anxiety and Depression Scale (HADS). The instrument has been used to measure anxiety and depression in BC patients. HADS comprises anxiety and depression subscales with seven items per subscale. A total score of 0-7 is normal, 8-10 is borderline abnormal and 11-21 is abnormal. This instrument has been validated and also found to be reliable with a Cronbach’s α coefficient of 0.79 for the anxiety subscale, 0.87 for the depression subscale, and 0.85 for all the items in an investigation into the psychometric properties in a previous study among BC patients (Rodgers et al., 2005) (See Appendix E).

*Symptom distress*

Symptom distress will be measured with the M. D. Anderson Symptom Inventory (MDASI) which comprises 13 items to measure symptom severity and six items to measure the rate of interference of the symptoms with patient’s activities of daily living. The symptom and interference items have been used in BC studies have been validated and found reliable with a Cronbach’s α coefficient of 0.85 and 0.91, respectively. (Cleeland, 2000). (See Appendix F).

*Quality of life*

Quality of life will be assessed using the Functional Assessment of Cancer Treatment-B (FACT-B). This instrument contains 37-items for measuring five domains of health-related quality of life in BC patients on a 5-point Likert scale with an alpha coefficient (internal consistency) of .90 (Brady et al., 1997). The total score for the five domains ranges from 0-148 with higher scores indicating better quality of life (See Appendix G).

***Demographic data sheet***

Demographic data will be collected on age, marital status, ethnic group, religion, level of education and occupation with a self-designed demographic data sheet (See Appendix H).

***Data collection***

The data collection will be conducted by two research assistants. Quantitative data will be conducted at baseline and immediately after the completion of the programme while qualitative data will be collected immediately after the programme completion. Data collection will be done at the oncology clinic. An information sheet which contains details of the intervention will be administered (Appendix I) after which the consent form will be completed (Appendix J).

The recruitment capability will be measured by documenting the recruitment rate, consent rate, and refusal rate based on the number of patients who are screened, those who are eligible, those who finally agree to be part of the study, and those who sign the informed consent form. Their reason for ineligibility and refusal to be part of the study will also be documented.

The acceptability and feasibility of the intervention will be assessed by documenting the attrition rate and the reason for lost to contact, adherence rate based on the number of participants that fully adhere to the protocol and data collection procedure, reasons for not adhering and any other adverse occurrence will be noted.

The acceptability of the intervention wi also be measured by a qualitative data collection. Three sessions of online, synchronous (live) focus group discussions with five participants in each group will be conducted by the research assistants. Online focus group discussion was considered appropriate for this part of the study due to its cost-effectiveness, no time commitment required for the participants to travel to the facility, ease of moderation and compatibility with the overall study design which is an online-delivered intervention (Rezabek, 2000). Questions for focus group interview in this phase is found in Appendix K. The focus group interview will explore the participants’ comments on acceptability of the intervention, ease of usage of the intervention and perceived usefulness of the intervention. Their findings will be used to improve the main intervention.

***Data analysis***

The quantitative data will be analysed using the SPSS version 25. The demographics and data related to intervention acceptability and feasibility will be analysed through descriptive statistics including frequencies, percentages, mean and standard deviation. Qualitative data will be analysed using NVIVO version 12. Thematic analysis will be conducted.

**MAIN RCT**

**Study design**

This study will be a multicentre RCT. This design was chosen for this study because RCTs are considered gold standard of experimental designs (Fewtrell et al., 2008) as they allow for random allocation which ensures equalisation of possible causes for intervention effects while allowing all subjects to have an equal chance of being assigned to a particular group (Polit & Beck, 2012). Also, RCTs help to establish the presumed cause-and-effect relationship between the study intervention and the outcomes which will help to generate knowledge that will be useful in clinical practice (Glasgow et al., 2003).

**Study setting**

Participants will be recruited from the oncology centers of Lagos State University Teaching Hospital (LASUTH), Ikeja and Lagos University Teaching Hospital (LUTH), Idi-Araba, Nigeria. At each hospital, approximately 50 women undergoing BC chemotherapy attend each center per month and an average of 25 of them have access to a smartphone and internet access.

**Sample**

Inclusion and exclusion criteria will be the same as the pilot study described in the previous phase.

***Sample size planning***

Sample size is calculated based on the primary outcome of self-efficacy. Power analysis was done with G*Power version 3.1 (Faul et al., 2007), and a medium effect size of 0.53 which was demonstrated in a previous mHealth psychoeducational study featuring women undergoing BC chemotherapy. Power was 0.8 and *p*<.05 with 10% attrition which was an average attrition rate found from a recent mhealth systematic review conducted on this population (Cohen 1988; Zhu et al., 2018). Sample size is estimated to be 126 participants, but the exact number will be confirmed after the pilot study.

**Outcomes measures**

The outcome measures will be the same as described in the pilot study.

**Fidelity of the intervention**

Fidelity of intervention refers to the degree of adherence to intervention protocol (Stein et al., 2007). To ensure fidelity in this study, the PI will obtain a certificate after participating in a training for health workers on psychoeducation for BC patients. The PI will also deliver all the sessions of the intervention. monitor and reinforce adherence to the program alongside provision of psychological support. This will ascertain consistency in the mode of delivery. The co-researchers that are experienced nurses working in the oncology units of the hospitals will provide nurse-consultancy services. The attendance rate of and response rate to the intervention will be monitored by the RAs. A personal link will be shared individually with the eligible participants to access the application. This link will be revoked after they are added. To prevent contamination, they will be instructed not to share the intervention content with any other patient. Process evaluation will be done to assess the fidelity of the intervention.

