This component addresses the ‘performance accomplishment’ construct of the self-efficacy theory. As the participants are taught coping skills, and they successfully implement these skills; this will bring a feeling of ‘performance accomplishment’, which will improve their self-efficacy to cope with the demands of the chemotherapy experience. Similarly, as the participants learn coping skills based on positive re-interpretation, acceptance, and spirituality, a positive emotion will be induced which will improve their coping with the chemotherapy experience. The participants will be expected to read and/or watch the coping skills training content within the week of posting.

- *Discussion forum*

As found in the systematic review (Hou et al., 2020; Lepore et al., 2014; Zhu et al., 2018), the discussion forum will feature discussion topics from the education, and this will be divided into sessions of six weeks and moderated by the researcher. Discussion forum in the mPEI programme will address the ‘vicarious experiences’ construct in the self-efficacy theory. As the women interact on the platform and share their success stories in adjusting and coping with the chemotherapy experience, this will encourage others and they will be motivated to complete the task which is successfully completing the chemotherapy.

The discussion forum will be implemented real time and non-real time. The real-time discussion will be at a time agreed on by the participants. Those that are not online at that time can leave further comments on various issues raised at their convenient time. The participants will be free to use a name they are comfortable with so their identity can be confidential. Similarly, they will not be required to display their pictures to maintain privacy. There will be six discussion groups in all with each group containing an average of 10 members as evidence suggests that this number allows for meaningful interaction and group administration (Biggs et al., 2020). The discussion forum will feature through the six weeks of the intervention.

- *Nurse-led consultation*

This will provide a means of answering questions and supporting participants in terms of their informational and psychological needs. This function will be provided by the oncology nurse designated for each participant through a 15-20-minute call in the first week, third week and fifth week.

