This component will address the ‘verbal persuasion’ construct of the self-efficacy theory. As the participants consult the nurses, they will receive verbal encouraging feedbacks that will support them through the chemotherapy experience.

- *Psychological Support*

The psychological challenge experienced by women receiving breast cancer chemotherapy varies depending on her temperament, her other burdens, and psychological history (Greenberg, 2010). Psychological support will be provided by actively listening to the participants, provision of a means to verbalize worries and concerns, and providing informational support. The psychological support will be given on an individual basis through the nurse-consultation function. This will entail 15-20 minutes call first week, third week and fifth week by oncology nurses from the research team.

This component will address the ‘emotional arousal’ construct of the self-efficacy theory. The fear of cancer and the chemotherapy experience will be controlled through the psychological support. As fear is controlled, anxiety will be reduced and self-efficacy to cope with the chemotherapy experience will increase.

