***Participant recruitment***

The co-researchers who are nurses in the oncology units will introduce the mPEI programme to eligible women. For those interested, their eligibility will be confirmed by the co-researchers. They will be given detailed information about the study after which their consent will be sought to join the study. For those that consent, they will be required to complete and sign a consent form.

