***Blinding***

The RAs will be blinded alongside the healthcare team. The patients will be aware of the intervention they are receiving, likewise the intervener (the researcher) will also be aware of the intervention; hence, they will not be blinded.

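### The protocol declares the healthcare team blinded, but nurses working in the oncology units deliver the intervention calls and so know who is in the intervention arm

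*Protocol*

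**What the plan says.** The Blinding section of the main trial states: "The RAs will be blinded alongside the healthcare team". It then gives the exceptions. Patients will know what they receive, and "likewise the intervener (the researcher) will also be aware of the intervention; hence, they will not be blinded". Nobody else is named as unblinded.

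Other sections say who delivers the individual part of the programme:

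- Fidelity of the intervention: "The co-researchers that are experienced nurses working in the oncology units of the hospitals will provide nurse-consultancy services".
- Components and contents, on nurse-led consultation: "This function will be provided by the oncology nurse designated for each participant through a 15-20-minute call in the first week", repeated in the third and fifth weeks.
- Components and contents, on psychological support: "The psychological support will be given on an individual basis through the nurse-consultation function".
- Intervention dosage: "psychological support and nurse consultation will be 15-20 minutes call first week, third week and fifth week by oncology nurses from the research team".

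The Participant recruitment section gives the unit-based co-researcher nurses a further task, which covers women before they are assigned to either arm: "For those interested, their eligibility will be confirmed by the co-researchers".

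Controls receive standard care alone. The Control Group section describes it thus: "For each hospital, standard care will entail routine care by doctors and nurses during their clinic attendance". It includes about 15 minutes of education at each attendance.

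The contamination measures are a personal app link that is later revoked and a no-sharing instruction to participants (Fidelity), with privacy and password instructions to participants added under Ethical considerations.

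**The concern.** A blinding statement tells readers which people could not have acted on knowledge of allocation. Here it covers a group that includes some of the people delivering the intervention. If it stands, the trial will report a protection that its design does not provide.

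Two practical risks follow. Unit nurses who know allocation could mention it to colleagues or to the research assistants who collect the data. They could also, without meaning to, carry programme material over to control women attending the same hospitals. The protocol recognises contamination as a risk, but its safeguard speaks only to participants and gives the calling nurses no instruction. The planned process evaluation could describe such events afterwards but would not prevent them.

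**Working it through.** The check is a comparison of sections. Arithmetic enters only for scale.

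1. **Who is declared blinded.** The research assistants and the healthcare team, with no carve-out for any nurse (Blinding).
2. **Who is declared unblinded.** The patients and one intervener, described in the singular as the researcher (Blinding). Intervention delivery has the principal investigator give the education and coping sessions and moderate the discussions, so the singular fits that role. It does not naturally cover several nurses at two hospitals.
3. **Who makes the calls.** Oncology nurses belonging to the research team (Components and contents; Intervention dosage). Fidelity and Participant recruitment both place the co-researcher nurses in the hospitals' oncology units, so they are research staff and unit staff at once.
4. **Does making a call reveal allocation?** Yes. The calls are a programme component and controls receive standard care only (Control Group; Randomisation). A nurse who makes a programme call knows the woman is in the intervention arm.
5. **Can control status be inferred?** Possibly. The co-researcher nurses confirm eligibility, so as a group they could work out that an enrolled woman whom none of them calls is a control. This is an inference; the protocol does not say that they are told.
6. **Who is bound by the contamination measures?** Participants. The instruction under Ethical considerations is wider than the one under Fidelity, because it covers anyone outside the intervention and not just other patients. It is still addressed to participants. No section addresses the nurses.

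**Scale.** The planned total is 126 with 1:1 allocation (Sample size planning; Randomisation), so 126 / 2 = 63 women per arm. Psychological support is given through the consultation, so this is read as one shared call on each occasion: 63 × 3 = 189 calls. The protocol leaves the total to be confirmed after the pilot, so both figures are provisional. At least one unit nurse would know the allocation of every woman in the intervention arm.

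**The case against.** The strongest reply is that the protocol does not define the healthcare team. The callers are described as co-researchers and as coming from the research team, and the Blinding section already treats the researcher as unblinded. On that reading the term means treating staff outside the research team, and nothing conflicts. The reading is possible, but the protocol never states it. Two sections place these nurses in the oncology units, and the list of unblinded people omits them. If that was the intention, the remedy is the same: say so.

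A second reply is that little depends on it. Every outcome is a patient-completed scale, patients know their arm, and no clinician rates an endpoint. This stands, and it limits the consequence: relisting the nurses changes neither the analysis nor the sample size. It does not make the statement correct.

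A third reply is that contamination is conjecture. This also stands. A reader might infer that the calling nurses educate control women, that programme content therefore reaches them, and that power falls. The protocol does not support that chain. It does not say that the callers give the clinic education, and it provides neither staffing overlap nor a contamination rate. Much of the programme is delivered through a link-restricted app and sessions led by the principal investigator. Any power loss calculated from this would rest on invented inputs.

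**Conclusion.** The point holds as a misstatement of blinding together with a gap in a safeguard that the protocol already has. Some oncology-unit nurses necessarily know the allocation of the women they call, so the claim that the healthcare team is blinded is wrong as written. This rests on two facts in the text: the callers work in the units, and only the intervention arm is called. It does not depend on any assumption about contamination.

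The reach is the whole intervention arm, about 63 women at the planned size. The effect on the trial's estimates cannot be quantified from the protocol and is probably limited, given patient-reported outcomes and unblinded patients. No change of sample size follows.

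A reader might also infer that all unit staff are unblinded. The text supports this only for the nurses who make calls. Nor does correcting this half of the sentence confirm the other half. Technical Support and Fidelity give the research assistants tasks with the intervention group (app training, and monitoring of attendance and response), so their blinding is a separate question that this point does not settle.

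**What to change.** **Blinding section.** List the co-researcher nurses who make the calls as unblinded, beside the patients and the principal investigator. Limit the healthcare-team claim to treating staff who do not deliver any part of the intervention. Word the change so that it does not imply that research-assistant blinding has been verified.

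**Fidelity section.** Extend the contamination instruction from participants to the calling nurses. They should not disclose allocation to colleagues or research assistants, and should not use app or programme materials with control women. Usual care for controls, including the clinic education, stays otherwise unchanged.

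**Cost.** Edits to two sections and a short instruction to the nurses, with no extra patients, contacts or data. The blinding statement becomes less favourable, and the safeguard depends on the nurses following the instruction.
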